## Abstract

**Background:**

Early palliative care along with standard cancer treatments is recommended in current clinical guidelines to improve the quality of life and survival of cancer patients. This study protocol aims to evaluate the effect of “Enhanced Supportive Care”, an early primary palliative care provided by nurses.

**Methods:**

A randomized controlled trial (RCT) will be conducted including advanced cancer patients scheduled for first-line palliative chemotherapy (*N*=360) and their caregivers in South Korea. Participants will be randomly assigned to the intervention or control group in a 1:1 ratio. Participants in the intervention group will receive the “Enhanced Supportive Care”, which provides five sessions of symptom management and coping enhancement counseling by nurses. The control group will receive symptom monitoring five times. The primary endpoints are symptoms, coping, and quality of life (QoL) at 3 months. Secondary endpoints are symptoms, coping, and QoL at 6 months, depression and self-efficacy for coping with cancer at 3 and 6 months, symptom and depression change from baseline to 3 months, survival at 6 and 12 months among patients, and depression among caregivers at 3 and 6 months.

**Discussion:**

This RCT will evaluate the effects of “Enhanced Supportive Care” on symptoms, depression, coping, self-efficacy for coping with cancer, QoL and survival of patients, as well as depression of caregivers. It will provide evidence of a strategy to implement early primary palliative care provided by nurses, which may consequently improve cancer care for newly diagnosed patients with advanced stage cancer.

**Trial registration:**

ClinicalTrials.gov, NCT04407013. Registered on May 29, 2020, https://www.clinicaltrials.gov/ct2/show/study/NCT04407013. The protocol version is ESC 1.0.

## Background

The ultimate goal of care for advanced cancer patients is to improve quality of life (QoL). Supportive care refers to care aimed at improving the QoL of patients experiencing life-threatening diseases. Patients with advanced cancer suffer from various symptoms such as pain, fatigue, and depression, which are known to negatively affect the patient's quality of life [1–5].

The WHO defines palliative care as early recognition of pain, physical, psychosocial, and spiritual problems faced by patients and their families related to life-threatening diseases and improving the quality of life through faithful assessment and intervention [6].

Palliative care is not limited to the end-of-life phase. Early palliative care provided within 8 to 12 weeks of advanced cancer diagnosis demonstrated its effectiveness in managing depression and improving quality of life and survival [7–13]. Studies have reported that early palliative care moderates the influence of depression on survival [14–16]. Survival after receiving early palliative care is reported as 4.56 months, which is comparable to 3.43 months of survival from recently licensed new cancer medicines [10, 17]. Although providing supportive care would not reduce the actual burden on family caregivers [18, 19], it is known to ameliorate symptoms of depression experienced by family caregivers [20]. Clinical guidelines recommend providing early palliative care within 8 weeks of cancer diagnosis along with standard cancer treatment for advanced cancer patients [21–23].

The provision of early palliative care could be achieved by integrating primary palliative care into standard cancer care. Primary palliative care denotes basic features of palliative care such as basic symptom management to be delivered by any clinicians caring for advanced cancer patients [24, 25]. Clinical practice guidelines for quality palliative care suggest essential palliative care skills are needed by all clinicians [23]. To provide primary palliative care, any clinician, not just a palliative care expert, needs to play an active role in palliative care provision through education and training [26, 27]. Providing primary palliative care as a part of standard care will meet patients’ supportive care needs and identify those at need for specialist palliative care.

Difficulties in accepting the term ‘palliative care’ at times of advanced cancer diagnosis have been an issue. The term ‘Enhanced Supportive Care’ has been suggested by NHS England to differentiate it from supportive care, which means the care of patients receiving active treatment [28] and palliative care at the end of life [29]. “Enhanced supportive care” in the current study refers to ‘early primary palliative care’ provided by nurses at the staff level.

Symptom management is a major element of palliative care [27, 30]. Symptom management is suggested to promote coping with cancer among patients [31]. According to the study by Bischoff et al. [32], which analyzed topics of actual palliative care encounters, symptom management was the most commonly addressed issue (92% of initial care and 93% of follow-up care). Digital symptom monitoring during routine clinical encounters for palliative chemotherapy resulted in less decline in health-related quality of life, less frequent emergency room visits or hospitalizations, and extension of survival [33]. The second most frequently applied palliative care component was coping interventions, which were identified in 64.2% of encounters for palliative care [34]. Cancer patients who demonstrated negative coping experienced a higher level of depression, a significantly higher expression of major depressive episodes at 1 year after diagnosis [35], and a lower quality of life [36].

Nurses have played an important role in the interprofessional collaborations that provide palliative care [21, 22, 30]. The current study examined the effects of “Enhanced Supportive Care”, which was developed based on previous studies, a literature review, and expert opinions on symptom management and coping enhancement provided by staff-level nurses as primary palliative care. The “Enhanced Supportive Care”, comprising symptom management and coping enhancement counseling, will be provided during outpatient visits beginning with the time of advanced cancer diagnosis and during initial palliative chemotherapy cycles. Symptom management and monitoring will be provided according to evidence-based symptom management education. Coping enhancement counseling based on the principles of self-efficacy for coping with advanced cancer [37] and Acceptance and Commitment Therapy (ACT) [38] will be provided considering the role of coping on QoL [39, 40]. The effect of the “Enhanced Supportive Care” as early primary palliative care provided by nurses along with standard cancer treatment will be evaluated.

## Methods

### Aim

The aim of this randomized controlled trial was to compare “Enhanced Supportive Care” to symptom monitoring in terms of effects on advanced cancer patients’ symptoms, depression, coping, self-efficacy for coping with cancer, quality of life, survival, and depression in caregivers.

### Design

A randomized controlled trial will be conducted by randomly allocating participants in a 1:1 ratio to the intervention or control arm. Participants in the intervention arm will receive the “Enhanced Supportive Care” consisting of symptom management and five sessions of coping enhancement counseling, while control group participants will receive symptom monitoring only. This protocol followed the SPIRIT (Standard protocol items: recommendations for interventional trials) guidelines for reporting protocols [41] (Fig. 1).

**Fig. 1 Fig1:**
[figure not shown]
Study design

### Setting

Patients and their caregivers will be recruited from a single cancer center that belongs to a tertiary hospital located in Seoul, Korea.

### Participants

#### Inclusion criteria

**Patient:**Adults (age ≥ 19)Diagnosis of advanced cancerScheduled to receive first-line palliative chemotherapyEuropean Cooperative Oncology Group Performance Status ≤ 2**Caregiver:**Adults (age ≥ 19)Family caregivers of cancer patients who agree to participate in the study

#### Exclusion criteria

Those diagnosed with cognitive or psychiatric problems and receiving treatment

### Randomization and blinding

The random allocation sequence was developed by the principal investigator (PI) before initiating patient enrollment. Research nurses will enroll and allocate patients according to the predefined sequence. Stratified permuted block randomization will be used to assign participants in a 1:1 ratio to the intervention or control group. Strata include the type of cancer (lung, breast, colorectal, gastric, liver/biliary/pancreas, or other cancers), age and sex of cancer patients. The minimization method will be applied after enrolling 60% of the participants in each cancer group to balance group allocation. Blinding is not considered applicable based on the type of intervention provided.

### Intervention

The intervention will be “Enhanced Supportive Care”, consisting of 1) symptom management (symptom monitoring and management) and 2) coping enhancement counseling. The “Enhanced Supportive Care” sessions will be provided by nurses five times over three months. Administration of the sessions will take approximately 50 min per visit: 1) symptom management (20 min) + 2) coping enhancement counseling (30 min).

Fidelity of the intervention: Web-based symptom assessment and education application, symptom management education booklet for home use, and coping enhancement counseling protocols will strengthen the fidelity of the intervention.

Interventionist training and tracking: Before starting the intervention, a symptom expert (PI) will train research nurses in how to monitor symptoms and provide evidence-based symptom management education. A certified clinical psychologist will teach the principals of counseling and the third-wave psychotherapy Acceptance and Commitment Therapy (ACT) and train research nurses in coping enhancement counseling. Periodic retraining sessions will be held with a certified clinical psychologist.

### Web-based symptom management system

The “Cancer Symptom Management System” application for the iPad [42] was upgraded to a web-based application to improve access from multiple digital devices. The upgraded web-based "Cancer Symptom Management System" application was developed using Python 3.7 and the Django framework. Every chart was rendered using Chart.js (https://www.chartjs.org), a popular open-source JavaScript library for visualizing data. The Cancer Symptom Management system was designed so that users (researchers) had to log into access data. Patients’ symptoms will be monitored using the “Cancer Symptom Management System” on an iPad. The results from symptom monitoring will be presented as a colored bar graph to the patients’ oncologists. Anxiety and depression scores will be generated and presented along with the symptom bar graph (Fig. 2). The generated symptom bar graph and the anxiety and depression scores will be uploaded to the patients’ Electronic Medical Records (EMRs) for oncologists’ review. Symptom management education will be provided by research nurses based on the results of symptom monitoring reflecting patients’ needs, as per a previous study [42].

**Fig. 2 Fig2:**
[figure not shown]
Example of symptom and depression assessment results from the “Cancer Symptom Management System” application

### Coping enhancement counseling based on principals of social cognitive theory and ACT

Protocols for coping enhancement counseling were developed based on the principles of social cognitive theory [43] and ACT [38]. Social cognitive theory will be applied to promote patients’ self-efficacy for coping with cancer. Patients’ current coping strategies in dealing with issues facing advanced cancer treatment and their effectiveness will be identified. As a strategy for mastery enhancement, patient-identified effective coping strategies will be promoted for use as resources for coping with cancer.

The principles of the ACT will be applied to help patients accept current emotions and thoughts experienced with advanced cancer diagnosis while finding and seeking life values. Committed actions toward life values will be encouraged and practiced. Coping enhancement counseling will be patient-centered because the program will help patients understand and accept their emotions, thoughts, and life values and choose their own committed actions. Throughout the program, participants will be encouraged to understand themselves as subjects of life (Table 1).

**Table 1 Tab1:** Coping enhancement counseling for enhanced supportive care

Session	Theme	Contents
1	Introduction	∙ Introduction about the coping enhancement counseling ∙ Share patient experience: Change after cancer diagnosis and major emotions experienced
2	Current coping strategies in dealing with major emotions	∙ Check for changes in major emotions and reasons for change ∙ Current coping strategies in dealing with major emotions and its effectiveness ∙ Metaphor: Water jar with sand ∙ Mindfulness exercise ∙ Homework
3	Finding life values	∙ Check for changes in major emotions and reasons for change ∙ Current coping strategies in dealing with major emotions and its effectiveness ∙ Finding life values ∙ Mindfulness exercise ∙ Homework
4	Commitment toward life values	∙ Check for changes in major emotions and reasons for change ∙ Current coping strategies in dealing with major emotions and its effectiveness ∙ Commitment toward life values ∙ Metaphor: Passengers on the bus ∙ Metaphor: Chinese finger trap ∙ Homework
5	Moving out from mind and going back to life	∙ Check for changes in major emotions and reasons for change ∙ Current coping strategies in dealing with major emotions and its effectiveness ∙ Review of previous sessions ∙ Identify differences before and after the coping enhancement counseling participation ∙ Utilize currently working coping strategies ∙ Accept emotions and thoughts and committing toward life values ∙ Mindful exercise ∙ Farewell

### Study procedures

The intervention group will receive the “Enhanced Supportive Care” consisting of 1) symptom management web-based symptom management system using iPad at each clinic visit (20 min) and 2) coping enhancement counseling (30 min). The “Enhanced Supportive Care” will be provided by trained nurses for 5 times over 3 months. Control group participants will monitor symptoms using web-based symptom management system using iPad at each clinic visits for 5 times and their symptom report will be delivered to oncologist via EMR, whereas neither evidence based symptom management education (using iPad and booklet) nor coping enhancement counseling by research nurses will be provided.

Participants could withdraw from the study upon request, and those who transfer to different hospitals, whose condition is deteriorated for study participation will be withdrawn from the study. Upon patients’ withdrawal, caregiver will withdraw as well.

Double data entry will ensure the integrity of the data. Collected information will be coded and stored for security, and the data will be monitored every 6 months.

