### Endpoints

The primary endpoints are symptoms, coping, and QoL at 3 months. Secondary endpoints are symptoms, coping, and QoL at 6 months, depression and self-efficacy for coping with cancer at 3 and 6 months, symptom and depression change from baseline to 3 months, survival at 6 and 12 months among patients, and depression among caregivers at 3 and 6 months. Any withdrawal from adverse events related to the intervention will be recorded and reported.

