### Statistical analyses

Per-protocol analysis will be conducted for primary endpoints using data from completers at 3 months. Intention-to-treat analysis will be conducted using the imputed full analysis set as sensitivity analysis. Missing data from those who provided data other than baseline will be imputed using the last observation carried forward (LOCF) method for symptom and depression scores. SPSS Statistics (version 26, IBM Corp., Armonk, NY, USA), SAS (version 9.4, SAS Inc., Cary, NC, USA), R (version 4.0.2, Institute for Statistics and Mathematics, Vienna, Austria, www.R-project.org), and Mplus (version 8.4, MPLUS, Los Angeles, CA, USA) software will be used for data analysis.

Primary hypothesis: Advanced cancer patients who receive “Enhanced Supportive Care” (symptom management + coping enhancement counseling) will demonstrate fewer symptoms and better coping and QoL at 3 months (T5) compared to the control group of advanced cancer patients who receive usual care with symptom monitoring only.

Secondary hypothesis: Advanced cancer patients who receive “Enhanced Supportive Care” (symptom management + coping enhancement counseling) will demonstrate fewer symptoms and better coping and QoL at 6 months (T6), less depression, higher self-efficacy for coping with cancer at 3 months (T5) and 6 months (T6). Changes in symptoms and depression from baseline (T1) to 3 months (T5) will be different between the intervention and control groups. The intervention group will demonstrate longer survival at 6 months (T6) and 12 months (T7) than control group. Family caregivers of advanced cancer patients who receive “Enhanced Supportive Care” will demonstrate less depression than family caregivers of patients who were assigned to the control group at 3 months (T5) and 6 months (T6).

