#### Secondary endpoints

Independent t-test to evaluate intervention effect for patients’ symptoms, coping and QoL at 6 months, patients’ depression and self-efficacy for coping with cancer at 3 and 6 months, and caregivers’ depression at 3 and 6 monthsLinear mixed model to evaluate intervention effect for change in symptoms and patients’ depression from baseline to 3 monthsPearson correlation and multiple regression analysis to identify factors contributing to symptoms, depression, coping, self-efficacy for coping with cancer and QoLKaplan‒Meier curve and log-rank test to evaluate intervention effect on survival at 6 and 12 monthsCox proportional hazard regression to identify factors contributing to survivalPearson correlation analysis, mediation and moderation analysis, and structural equation modeling to understand relationships among symptoms, depression, coping, self-efficacy for coping with cancer, and QoL

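### Withdrawal for deterioration or transfer ends study participation for patient and caregiver alike, so survival is censored in a way linked to prognosis and caregiver depression is seen only where the patient stayed in.

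*Protocol article*

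**What the plan says.** All references are to the protocol article.

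- **Study procedures, patients.** Besides withdrawal on request, "those who transfer to different hospitals, whose condition is deteriorated for study participation will be withdrawn from the study". The consequence is leaving the study, not only leaving the sessions.
- **Study procedures, caregivers.** "Upon patients’ withdrawal, caregiver will withdraw as well". No exception is given.
- **Endpoints.** The secondary endpoints include "survival at 6 and 12 months among patients, and depression among caregivers at 3 and 6 months".
- **Statistical analyses, secondary hypothesis.** "The intervention group will demonstrate longer survival at 6 months (T6) and 12 months (T7) than control group".
- **Secondary endpoints (analysis).** Kaplan-Meier curves and a "log-rank test to evaluate intervention effect on survival at 6 and 12" months, with Cox regression for factors related to survival. Caregiver depression is compared by independent t-test.
- **Statistical analyses, missing data.** "Missing data from those who provided data other than baseline will be imputed using the last observation carried forward (LOCF) method for symptom and depression". This concerns questionnaire scores; nothing is said about survival times of withdrawn patients.

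The text shown does not say that vital status is still collected after withdrawal, or that a caregiver may stay on.

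**The concern.** Kaplan-Meier, log-rank and Cox methods assume that, within an arm, a patient censored at a given time has the same outlook as those still followed. A patient starting first-line palliative chemotherapy who becomes too ill to take part will usually have a worse outlook than one who continues. If follow-up for death stops there, the deaths that follow are not counted and the survival curve is too high.

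If the arms lose such patients at different rates, the comparison is biased as well. That is possible here: the trial is unblinded (Randomization and blinding), the article gives no criterion for deterioration, so the decision is a judgement, and only the intervention arm has the 50-minute sessions (Intervention).

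The caregiver endpoint has a related problem. A caregiver who is able and willing to complete the HADS is removed because of something that happened to the patient after randomisation, and which the intervention may influence. The t-test then compares subsets that randomisation no longer protects. Families in which the patient declined are under-represented, and they are plausibly the more strained ones.

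An analysis plan cannot repair this, because the rule stops the data from being collected.

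**Working it through.** **The plan's own figures.** There is none to reproduce on this point: the article gives no death count, hazard ratio, survival rate or power for survival, and no power for caregiver depression. Only two figures bear on it: 360 patients randomised 1:1 (180 per arm) and a 20% dropout allowance, 0.20 × 360 = 72 patients (Sample size determination).

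**Assumptions (not from the article).** Exponential survival, 60% at 12 months in the control arm, 12 months of follow-up. A share *p* of deaths is preceded by withdrawal 0.5 to 2 months earlier, with no vital status afterwards.

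**Hand approximation.** The observed hazard is about (1 − *p*) times the true one.

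- Deaths without loss and without effect: 360 × 0.40 = 144. With 25% lost, 108; with 50% lost, 72.
- 12-month Kaplan-Meier: 0.60^(1 − *p*). For *p* = 0.25, 0.60^0.75 = 0.68. For *p* = 0.50, 0.60^0.50 = 0.77.
- Apparent hazard ratio (intervention/control) with no true effect: (1 − *p*_int)/(1 − *p*_con). For 30% control and 20% intervention, 0.80/0.70 = 1.14. For 60% and 40%, 0.60/0.40 = 1.5.
- Power at a hazard ratio of 0.65: intervention survival is 0.60^0.65 = 0.717, so deaths are 180 × 0.40 + 180 × 0.283 = 123. With |ln 0.65| = 0.431, power = Φ(0.431 × √(D/4) − 1.96). D = 123 gives Φ(0.43) = 67%; D = 92 (25% lost) gives Φ(0.11) = 54%; D = 61 (50% lost) gives Φ(−0.28) = 39%.

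**Simulation under the same assumptions** (ranges are across repeated runs; rejection at two-sided 0.05):

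| Deaths lost, control / intervention | True HR | Deaths seen | 12-month KM, control / intervention | Apparent HR | Log-rank rejection |
|---|---|---|---|---|---|
| 0 / 0 | 1 | 144 | 0.60 / 0.60 | 1.00 | 5% |
| 25% / 25% | 1 | 108 | 0.68 / 0.68 | 1.00 | 5% |
| 50% / 50% | 1 | 72 | 0.77 / 0.77 | 1.00 | 5% |
| 30% / 20% | 1 | 108 | 0.70 / 0.66 | 1.13-1.14 | 9-10% |
| 55% / 45% | 1 | 72 | 0.79 / 0.75 | 1.2 | 12-14% |
| 60% / 40% | 1 | 72 | 0.81 / 0.73 | 1.5 | 38% |
| 0 / 0 | 0.65 | 123 | 0.60 / 0.72 | 0.65 | 66-67% |
| 25% / 25% | 0.65 | 92 | 0.68 / 0.78 | 0.65 | 53-55% |
| 50% / 50% | 0.65 | 61 | 0.77 / 0.85 | 0.64-0.65 | 40-41% |

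**How far these shares strain the plan.** Losing 50% of deaths means about 21.5% of patients withdrawn by month 12, slightly above the whole 20% allowance. Losing 25% means about 11%, roughly half of it.

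**Sensitivity to the assumptions.** With 50% true 12-month survival and withdrawal 0 to 4 months before death, equal loss of 20% or 40% gives a 12-month estimate of 0.57 or 0.65. With no true effect, 40% control against 20% intervention gives a hazard ratio of 1.29 (type I error 30%); reversing the arms gives 0.77. Over true survival of 30% to 70% these are 1.29-1.31 and 0.76-0.78. So the bias can run either way.

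**Caregivers.** No arithmetic applies. A caregiver whose patient is withdrawn before 3 months contributes to neither assessment; one whose patient is withdrawn between 3 and 6 months contributes only to the first.

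**The case against.** The strongest reply is that censoring of survival is inferred, not stated. The article does not say how vital status is obtained, the assessment schedule is in a figure that is not shown, and a condensed article may leave this to the full protocol. If deaths are taken from records whatever the participation status, the survival part disappears. This stands as a limit on certainty. But the rule is stated without exception and sits beside a 12-month survival endpoint, so the text needs a sentence either way. The caregiver part does not depend on it.

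Several stronger readings are tempting and not supported:

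- *That those withdrawn are the patients about to die.* The criterion is being too ill to take part, and transfer to another hospital need have nothing to do with prognosis.
- *That the log-rank result will be false.* With equal loss the hazard ratio stays near 1 and type I error near 5%. Bias between arms needs unequal loss, for which the article gives no evidence. The largest figures above also use up the whole dropout allowance on patients close to death, leaving none for requests or unrelated transfers.
- *That caregiver depression is measured only where the patient did well.* Caregivers of ill patients who remain in the study are measured. Carrying the last depression score forward may also retain, in the imputed analysis, some caregivers who gave 3-month data. It does not help those who leave before 3 months.

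Enrolling and withdrawing patient and caregiver as a pair is also a defensible design choice. Keeping caregivers on would bring bereaved caregivers' scores into the endpoint, which needs a rule of its own.

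**Conclusion.** The concern holds as a conflict between a stated withdrawal rule and two stated secondary endpoints. Followed literally, the rule censors survival at a time linked to prognosis and limits caregiver depression to caregivers whose patient was not withdrawn.

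The size cannot be derived from the article. Under the main set of assumptions, equal loss of 25% to 50% of deaths overstates 12-month survival by 8 to 17 percentage points (0.68-0.77 against 0.60) and costs about 12 to 27 points of power at a hazard ratio of 0.65, without invalidating the test. Unequal loss ranges from a modest distortion (30% against 20%: hazard ratio 1.13, type I error 9%) to a severe one (60% against 40%: about 1.5 and 38%). The severe end is close to a worst case.

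This should be fixed, but it does not by itself undermine the trial: both endpoints are secondary, and how vital status is obtained is not stated. A reader might extend the point to the primary endpoints, since the same rule adds to missing 3-month data. The weakness there lies mainly in the choice that "Per-protocol analysis will be conducted for primary endpoints using data from completers at 3 months", which is a separate matter.

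**What to change.** Amend Study procedures so that stopping the sessions and leaving the study are different events.

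1. Deterioration or transfer ends the sessions as now planned, but not follow-up. Nothing in when or why sessions stop needs to change.
2. Ascertain vital status to 12 months for every randomised patient unless consent is withdrawn, state the source, and analyse survival in all randomised patients. If this is already done, say so; the survival part is then settled.
3. Delete the automatic caregiver withdrawal. Let willing caregivers complete the HADS at 3 and 6 months, identify bereaved caregivers, and handle their scores by a rule fixed in advance.
4. Record the date and reason of each withdrawal by arm, so that any imbalance can be seen.

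**Cost.** A short protocol, consent and ethics amendment, and record look-ups. Recruitment began in March 2021, so the change falls within the trial: retrieving vital status for patients already withdrawn needs ethics approval, and caregiver scores already missed cannot be recovered. If questionnaires are completed remotely, the collection mode changes part-way through and should be recorded for each assessment.
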